#### Secondary objectives

We will characterize all secondary endpoints descriptively. All secondary methods will be analyzed with standard methods (e.g., *t*-test, Wilcoxon Mann–Whitney test, chi-square test, etc.), depending on their scales (metric vs. non-metric data). All secondary objectives are considered exploratory with limited inferential value. We will apply prediction modeling with measures of performance (accuracy/calibration) to study the diagnostic or prognostic value of novel markers for etiology determination and outcomes.

#### Potential bias and methods to reduce bias

Since this study is observational and thus randomization and masking to treatment assignment are not possible, it has potential sources of the known bias. First, the study has a selection bias, as some people do not present in the clinic for an inaugural ON at all or are more likely to present with a more severe ON. To mitigate this, a patient's medical history is assessed in a semi-standardized way to detect potential previous attacks, leading to study exclusion. In addition, an ophthalmological examination is conducted to assess for evidence of prior ON damage. Furthermore, prior polling of participating centers carried out in 2021/2022 regarding the number of patients with acute ON seen in each clinic demonstrates the feasibility of including a representative population of subjects with inaugural ON of all severities.

Second, the study has a confounder bias, as subjects will receive treatment according to their time of presentation at the hospital as the standard of care. Furthermore, disease-modifying treatments and other medication initiated between the baseline and follow-up will be analyzed as potential confounders. While high-dose corticosteroid treatment cannot be delayed for ethical reasons, a thorough record will keep the process transparent, and confounders will be minimized by advanced biostatistical techniques, such as confounder adjustment.

Information bias may be introduced when recording the primary visual outcomes, stemming from differences in visual acuity recording techniques, room lighting, and different physicians measuring visual acuity. Therefore, a training course for all participating centers will be held, which aims to standardize assessments across centers. To overcome analytic differences within different OCT machines, we have developed a pipeline for device-independent intraretinal layer OCT segmentation (74), allowing for standardized analysis regarding the region of interest and layer boundaries. Additional potential biases include OCT-captured artifacts for which ACON agreed to adhere to the APOSTEL guidelines for performing and reporting OCT measurements (75). Similarly, different MRI techniques pose another source of information bias. To counteract this, ACON will offer short MRI evaluation training to the participating centers, focusing on the interpretation of optic nerve abnormalities.

To overcome biases through assay differences, blood and CSF samples will be stored to perform centralized testing during follow-up.

## Discussion

ACON is the first global prospective longitudinal study on acute ON that includes participating centers from Africa, America, Asia, Australia, and Europe. It intends to build up a comprehensive, systematic, multimodal database of ON patients both in the acute phase and during longitudinal follow-up. Since the publication of the ONTT results in 1992 (21), no large-scale international multicenter study has investigated the treatment of acute ON. In particular, the effect of time to treatment on visual outcomes has not been examined prospectively, either in a multi-racial cohort or with regard to different ON etiologies. Therefore, clinical treatment decisions are largely based on individual choices but lack scientific evidence. ACON will address the question of the potential benefit of hyperacute high-dose corticosteroids on visual acuity, visual function in daily routine, QoL, and optic nerve structural outcomes in acute MS-ON, AQP4-IgG+ON, and MOG-IgG+ON. ACON will investigate the viability of early clinical clues as potential indicators, both for the underlying diagnosis and the respective disease course. The medical history is the first step in the diagnostic workup. To investigate pain scores as a means of distinguishing MS-ON and AQP4-IgG+ON from MOG-IgG+ON, we will carry out a semi-structured interview to assess the chronology of visual symptoms and characterize pain patterns. Data obtained from this interview, collected from multiple countries, including a wide range of races, are expected to result in an easily accessible clinical tool to accelerate the diagnosis with regard to etiology. Furthermore, ACON aims to explore the implications of early dynamics in levels of NfL and GFAP in the serum of patients with acute ON and their potential prognostic value for a subsequent disease conversion to MS, NMOSD, and MOGAD. MRI of the brain and the spinal cord plays an essential role in the diagnosis of these three diseases. For example, prior studies could show that the combination of two radiologic parameters (e.g., absence of brain abnormalities and a greater lesion extension) offers a valuable tool to discriminate between MS-ON and antibody-associated ON (28, 76). Furthermore, a recent study shows that the length of optic nerve inflammation seen in MRI correlates with retinal neuro-axonal loss and chronic visual impairment (29).

ACON will have the potential to provide information about the interrelation between MRI-based lesion characteristics and clinical symptoms, the duration of contrast enhancement, and predictors of the respective diagnosis.

OCT is the method of choice to measure precisely the thickness of retinal layers and to detect structural damage (77, 78). Axonal degeneration begins on a molecular level, within hours of ON onset and can be reliably quantified by OCT after ~3 months (6, 79, 80). OCT-derived retinal measurements have been used as structural biomarkers for disease progression and tissue damage in MS and related disorders (74, 81–88). Thinning of the combined ganglion cell–inner plexiform layer (GCIPL) in non-ON eyes of people with CIS and early MS is associated with future MS disease activity (84, 85). However, there is no such investigation in acute ON. Prior studies from our groups have shown that cumulative axonal damage, macular GCIPL thinning, and visual loss are typically more severe in AQP4-IgG+ON than in MS-ON and MOG-IgG+ON (89–91), and higher grade pRNFL swelling is closely correlated with MOG-IgG+ON in distinction to MS-ON (30).

ACON will investigate the ability to predict the development of clinically manifested MS through acute OCT parameters including pRNFL and macular ganglion cell analysis, as well as advanced parameters such as the shape of the optic nerve head (92).

ACON provides a global effort for collecting real-world information and high-quality prospective multimodal data on subjects with acute ON from 28 participating centers across six continents. It focuses on the longitudinal observation of subjects with MS-ON, AQP4-IgG+ON, and MOG-IgG+ON. With a better understanding of these distinct neuroimmunological conditions, ACON aims to accelerate ON diagnosis and establish acute ON treatment standards that are applicable globally.

Moreover, the ACON study will provide invaluable insights into the course of these diseases. Particularly, ACON has the capacity to give novel insights into MOGAD for which the proportion of monophasic vs. relapsing cases is far from clear (8). Given a follow-up of 12 months minimum (a longer observation period is envisioned), the study will also generate data on the implementation of preventative immunotherapy (when to treat, whom to treat, and potentially which drug to use?). While there is broad consensus that immediate immunotherapy after diagnosis is indicated in AQP4-IgG+NMOSD given the high risk of recurrence and poor prognosis if left untreated (93–95), the situation is less clear in MS and MOGAD (96, 97), and finally, in light of the rapidly changing treatment landscape with approved drugs for AQP4-IgG+NMOSD and several clinical trials in MOGAD currently underway, the ACON study will collect clinically useful data on individual treatment sequences for on-label or off-label immunotherapies in patients with acute ON (97–100).

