### Structural biomarkers as an aid to tailor ON treatment

To explore possible means to aid hyperacute treatment decisions, the ACON study will collect data on and evaluate the potential of structural biomarkers as methods to enhance timely diagnoses. These structural biomarkers will be explored using magnetic resonance imaging (MRI) and optical coherence tomography (OCT).

MRI of the brain and the orbits is one of the most established clinical tools for investigating acute ON. The radiological features of ON differ between the three disease etiologies: optic nerve lesions in AQP4-IgG+ON and MOG-IgG+ON are more frequently bilateral and more extensive than in MS-ON (26–28). AQP4-IgG+ON typically affects posterior parts of the optic nerve and the chiasm, while MOG-IgG+ON typically affects long segments of the anterior optic nerve (10, 28). During the acute phase of ON, optic nerve lesion length has been shown to be a useful imaging biomarker, predictive of retinal neuro-axonal loss and chronic visual impairment (29). We will explore the diagnostic and clinical relevance of visual pathway lesions and their persistence following the inaugural ON.

OCT with the peripapillary retinal nerve fiber thickness (pRNFL), the macular ganglion cell layer (GCL), or the ganglion cell complex (GCC) measurements aid differentiation between acute MS-ON and MOG-IgG+ON (30). However, age and race have been reported to impact pRNFL (31). We will re-explore whether pRNFL robustly differentiates MS-ON from MOG-IgG+ON in a multi-racial population of subjects with inaugural ON. Assessment of OCT imaging parameters such as the ganglion cell analysis may allow disease stratification and detection of subclinical activity prior to the initial ON and may provide insightful longitudinal data such as rate of progression, which has the potential to correlate with disease severity (32, 33).

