### Biological biomarkers

Neurofilament light chain (NfL) is a major structural component of neurons and can be detected in the serum and cerebrospinal fluid (CSF). Elevated NfL levels are an indicator of neuronal damage (34) in acute ON (35), coinciding with visual dysfunction (36) and structural retinal damage (37). However, the role of serum NfL levels and dynamics in the acute stage of ON as potential indicators for subsequent conversion to MS, NMOSD, or MOGAD remains unexplored.

Glial fibrillary acidic protein (GFAP) is the predominant intermediate filament in mature astrocytes (38, 39) and was identified in astrogliosis MS lesions (40). It is differentially elevated in the CSF and the blood in the three inflammatory diseases of interest in this study (41–43). ACON aims to collect data on NfL and GFAP in the serum and CSF of patients following acute ON and to investigate their patterns in MS-ON, AQP4-IgG+ON, MOG-IgG+ON and also in double-seronegative non-MS-ON.

The detection of serum MOG-IgG is a crucial step for correctly diagnosing MOGAD (44). Live cell-based assays (CBA) using full-length human MOG are optimal and have consistently shown a 99% specificity for typical MOGAD phenotypes (44, 45). Many centers worldwide use a commercially available cell-based assay using fixed transfected cells (Euroimmun AG, Lübeck Germany), which has excellent (98%) specificity (46). Titers of MOG-IgG can decrease to undetectable levels following an acute attack, after treatment or disease remission. Thus, potential factors affecting the duration of seropositivity will be explored using longitudinal serum samples from patients exhibiting MOG-IgG seropositivity following acute ON. The diagnostic value of CSF antibody testing remains unclear. Since AQP4-IgG and MOG-IgG are both produced extrathecally, testing CSF is currently not routinely recommended (47). However, a few cases of seronegative NMOSD have been described, where MOG-IgG was present in CSF only (48). ACON aims to clarify the role of MOG-IgG in CSF in double-seronegative non-MS-ON.

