## Methods and analysis

### Study objectives

The primary objective of ACON is to investigate whether MS-ON, AQP4-IgG+ON, and MOG-IgG+ON patients treated with early high-dose corticosteroids for visual loss have better visual outcomes than those with late treatment. Treatment with both IVMP and oral high-dose corticosteroids is currently used as the standard of care in ON and will be included. According to previous data (24), subjects will be stratified into three groups: those presenting within 3 days of the onset of visual loss, those presenting between 4 and 7 days from the onset of visual loss, and those presenting between 8 and 30 days from onset of visual loss (days-to-Rx). The stratification will be performed within each respective disease group (MS, AQP4-IgG+NMOSD, and MOGAD).

Secondary objectives will consist of the interaction between clinical and para-clinical parameters, as well as their association with patient-reported QoL aspects (see Table 1; Figure 2).

**Table 1 T1:** Secondary objectives.

• Visual and structural outcomes of acute ON in patients treated with high-dose corticosteroid-therapy vs. plasmapheresis as first-line treatment.
• Visual and structural outcomes of MS-ON in patients treated with high-dose corticosteroid-therapy with oral prednisone taper vs. without taper as standard of care.
• Diagnostic and prognostic value of biomarker levels (NfL, GFAP) and associations with visual pathway damage (MRI- and OCT-based) in the acute stage and during follow-up.
• Characterization of MOG-IgG and AQP4-IgG levels and compartmentalisation (serum vs. CSF, using simultaneous paired samples) and associated risks for subsequent relapses in subjects with AQP4-IgG+ON and MOG-IgG+ON.
• Diagnostic value of OCT markers (e.g., increased pRNFL) for diagnosis of MS, NMOSD, and MOGAD.
• Prognostic value of OCT markers (e.g., increased pRNFL) for the visual outcome at 12-months follow-up.
• Diagnostic value of OCT markers for a conversion from acute ON to clinically definite MS.
• Diagnostic value of early clinical variables (i.e., visual loss and pain patterns).
• Investigation of the link between clinical symptoms (i.e., degree of visual loss and pain patterns) and lesion extension (detected using MRI and OCT).
• Characterization of visual function in daily routine, visual QoL scores and incidence of depression at 12-months follow-up.
• Interrelation of HC-BCVA and LC-BCVA and patient reported outcome measures at 6- and 12-months follow-up.

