### Biosampling

Blood and CSF will be collected within one week from the presentation. Venous blood samples will be collected, comprising of serum, plasma, as well as optional PAXGen and peripheral blood mononuclear cell (PBMC) vials. Biosample analysis includes a clinical standard laboratory diagnostic panel as well as testing for AQP4- and MOG-antibodies, GFAP, and NfL. Systematic serum antibody measurements including AQP4-IgG and MOG-IgG will be performed with fixed or live cell-based assays (CBA) (65–67). MOG-IgG samples will be tested and reconfirmed employing both the commercially available assay and the human cell-based assay. Cell-based assays for MOG-IgG will either be performed at centers at which this assay is available (Mayo clinic, Barcelona, etc.) or shipped to a participating ACON center to reconfirm fixed cell-based assays.

CSF will be obtained from clinical routine diagnostics (only in the acute phase) and collected for further analysis at the respective center. Routine diagnostics include oligoclonal band detection and cell count. In addition to a clinical standard CSF analysis, MOG-IgG in CSF will be assessed. Preserves of biospecimens will be stored at −80°C for future scientific analyses.

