### Optical coherence tomography

Participants will undergo OCT of the retina and the optic nerve head within 10 days from the presentation. The following Spectral Domain OCT devices will be included: Cirrus HD-OCT, Carl Zeiss Meditec, Jena, Germany; Topcon, Optovue, Canon or Spectralis, Heidelberg Engineering, Heidelberg, Germany.

Scans will be obtained in adherence to the Advised Protocol for OCT Study Terminology and Elements (APOSTEL) 2.0 nine-point recommendations and the OSCAR-IB quality criteria (68, 69). Documented OCT measurements include the average pRNFL thickness, GCL or GCC as collected by the different platforms (e.g., Spectralis measuring GCL, Zeiss measuring GCC). The OCT images will subsequently be analyzed using *post-hoc* analysis with semi-automatic, device-independent algorithms (70).

We will exclude patients with insufficient documentation or those who have their OCT imaging on time-domain devices. Low-quality spectral-domain OCT data will be excluded from the OCT analysis. We plan to qualitatively explore concomitant OCT findings, including microcystic macular oedema (MMO) or peripapillary hyperreflective ovoid mass-like structures (PHOMS) (71, 72).

Table 3 summarizes the data collection.

**Table 3 T3:** Data collection overview.

**Collected data type**	**Study Enrollment (Screening)**	**Baseline**	**6 months follow-up**	**12 months follow-up**	**Additional study visits (optional)**
Patient demographics	X				
Informed consent	X				
Inclusion/exclusion criteria	X				
Race		X			
Semi-structured assessment of patient reported visual symptoms		X	X	X	(X)
Semi-structured pain assessment		X	X	X	(X)
Treatment history		X	X	X	(X)
Medical history and comorbidities		X	X	X	(X)
Pregnancies		X	X	X	(X)
Vaccination history		X	X	X	(X)
Relapse history		X	X	X	(X)
BPI		X	X	X	(X)
BDI-II		X	X	X	(X)
EQ-5D		(X)	(X)	(X)	(X)
Visual function in daily routine (NEI-VFQ-25 + neuro-ophthalmological supplement)		(X)	(X)	(X)	(X)
Vital signs and measurements		X	X	X	(X)
Clinical routine laboratory tests from serum and CSF, including OCB, AQP4-IgG, MOG-IgG		X	X	X	(X)
Biomarker analysis (GFAP, NfL)		X	X	X	(X)
EDSS		X	X	X	(X)
High-contrast visual acuity		X	X	X	(X)
Low-contrast visual acuity		X	X	X	(X)
Automated visual fields (24-2 or 30-2)		(X)	(X)	(X)	(X)
VEP		(X)	(X)	(X)	(X)
Cerebral MRI, including orbital cuts (lesion number, lesion volume, lesion location, number of involved segements by the ON)		X	(X)	(X)	(X)

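### The mandatory schedule gives one acute NfL/GFAP sample, timed from presentation, so it cannot supply early dynamics for the cohort, and marker comparisons need adjustment for sampling time and prior corticosteroids

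*Protocol article*

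**What the plan says.** The aim at issue stands in the Discussion: "ACON aims to explore the implications of early dynamics in levels of NfL and GFAP in the serum of patients with acute ON", together with their possible value for predicting which disease follows. The listed secondary objective (Table 1) is "Diagnostic and prognostic value of biomarker levels (NfL, GFAP) and associations with visual pathway damage (MRI- and OCT-based) in the acute stage and during follow-up". Other objectives in Table 1 concern the diagnostic and prognostic value of OCT markers, with raised pRNFL as the example. The section on structural biomarkers gives the intended use: "To explore possible means to aid hyperacute treatment decisions".

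On timing, the Biosampling section says: "Blood and CSF will be collected within one week from the presentation". The OCT section says: "Participants will undergo OCT of the retina and the optic nerve head within 10 days from the presentation". Patients may enter up to 30 days after onset of visual loss (Study population). In Table 3, NfL/GFAP and OCT are mandatory at baseline, 6 and 12 months and optional at additional visits. Study design leaves those additional visits to patient need and local practice.

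On analysis, the Secondary objectives part of Statistical analysis names the t-test, Wilcoxon–Mann–Whitney and chi-square tests as examples, adds prediction modelling, and calls all secondary objectives exploratory. Analysis groups are formed from the diagnosis at 6 months.

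**The concern.** There are two linked problems.

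First, a within-patient early change needs at least two early values, and only one is scheduled. An analysis plan cannot supply samples that were not taken. Conclusions about early dynamics would rest on whichever patients happened to be sampled again, and that subset is selected by clinical need and by centre.

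Second, the one acute value is not tied to onset of visual loss or to the first corticosteroid dose. If patients with one diagnosis tend to present later, or are more often treated before the draw or scan, an unadjusted comparison of NfL, GFAP or pRNFL between diagnoses mixes disease with timing. The same applies between centres, where the mix of the three diseases differs, as the plan itself notes. A marker rule built on a mixture of pre- and post-treatment measurements may then not carry over to decisions made at first presentation.

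**Working it through.** The plan states no figure on this point, so there is none to reproduce. The check is a count of measurements and arithmetic on the windows.

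**Inputs**
- Entry: day 0 to 30 from onset of visual loss (Study population).
- Blood: 0 to 7 days from presentation (Biosampling). OCT: 0 to 10 days from presentation (Optical coherence tomography).
- Strata: 0–3, 4–7 and 8–30 days to high-dose corticosteroids (Sample size considerations).
- Mandatory visits: baseline, then 6 and 12 months after onset (Study design, Table 3).

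**Acute measurements per patient.** Mandatory: 1. Needed for a slope: at least 2.

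**Latest sampling day from onset** = latest entry day + collection window.
- Blood: 30 + 7 = 37, so days 0–37.
- OCT: 30 + 10 = 40, so days 0–40.

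**By stratum**, assuming that treatment starts on the day of presentation:

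| Stratum (days) | Blood (+7) | OCT (+10) |
|---|---|---|
| 0–3 | 0–10 | 0–13 |
| 4–7 | 4–14 | 4–17 |
| 8–30 | 8–37 | 8–40 |

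The ranges overlap and shift with the stratum, so sampling day moves with time to presentation.

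**Prior treatment.** The intravenous courses listed under Medical history and clinical examination last 3 or 5 days. Both are shorter than the 7-day and 10-day windows, so a baseline sample or scan may come before, during or after the course.

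**Gap to the next mandatory value.** Taking 6 months as 183 days from onset (assumption), the gap is between 183 − 37 = 146 and 183 − 0 = 183 days. That visit also assigns the diagnosis used for analysis. A change from baseline to 6 months is therefore not early, and it does not precede the 6-month diagnosis. It could still precede outcomes at 12 months.

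**Illustration of size (assumption only).** The documents give no rate of change for any marker and no difference in sampling day between diagnoses. If a marker drifted by 0.02 to 0.10 SD per day and two groups differed by 7 days in mean sampling day, timing alone would produce a difference of 0.02 × 7 = 0.14 to 0.10 × 7 = 0.70 SD. This shows how the effect scales and is not an estimate for this study.

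**The case against.** The case on the other side is substantial, and several stronger readings fail.

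- A reader might infer that the Introduction also promises acute dynamics. It does not. Its phrase "the role of serum NfL levels and dynamics in the acute stage of ON as potential indicators for subsequent conversion to MS, NMOSD, or MOGAD" belongs to a sentence describing what has not yet been studied. The Table 1 objective speaks of levels, which the three mandatory samples can serve. The mismatch lies in the Discussion sentence.
- A reader might infer that early dynamics cannot be studied at all. Table 3 permits NfL, GFAP and OCT at optional visits, so some patients may have repeat early values. What fails is coverage of the cohort.
- A reader might infer that early pRNFL dynamics are promised too. They are not, and only the timing point applies to pRNFL.
- A reader might argue that a scan as late as day 40 no longer captures swelling. No passage says so. The Discussion says only that axonal degeneration "can be reliably quantified by OCT after ~3 months", which does not show that thinning affects a scan by day 40.
- A reader might infer that the database lacks the dates needed. An article cannot show that. Days to corticosteroid treatment is a core variable, symptom chronology is taken by interview, and the case report forms are in a supplement that is not shown.
- Covariates are commonly left to an analysis plan, the list of tests is open-ended, and the objectives are declared exploratory. This stands as a limit on the weight of the point. It does not remove it. The text names unadjusted tests, and the general promise of confounder adjustment under Potential bias concerns treatment timing and medication started between baseline and follow-up. Sampling day and corticosteroids given before the baseline sample are not mentioned there.

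**Conclusion.** The point holds in a limited form. The mandatory schedule provides one acute NfL/GFAP value and the next about 146 to 183 days later, so it does not support the Discussion's aim for the cohort. Baseline values span days 0–37 (blood) and 0–40 (OCT) from onset and may be taken before or after corticosteroids. The analyses as named do not separate diagnosis from that timing.

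Any resulting distortion depends on two things the documents do not report: how fast each marker changes in the acute phase, and whether sampling day or prior treatment differs by diagnosis or centre. If neither differs, unadjusted group comparisons are not biased by timing, only noisier. The mixing can be repaired in analysis provided that the dates are kept. The matter is confined to exploratory secondary objectives, and the primary question on time to treatment and visual acuity is untouched.

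**What to change.** 1. In the Discussion, restate the aim as the acute level of NfL and GFAP and the change from the acute phase to 6 and 12 months. Describe any early repeat samples only as a selected subset.
2. In the Secondary objectives part of Statistical analysis, or in the analysis plan if one exists, analyse NfL, GFAP and pRNFL as diagnostic or prognostic markers with models that include days from onset to the draw or scan and pre-/post-corticosteroid status. For pRNFL add age and race, since the section on structural biomarkers says that both have been reported to affect it.
3. Confirm that the date of each draw and scan is captured relative to onset and to the first corticosteroid dose. Missing dates may be hard to recover later across 28 centres.
4. Add a sensitivity analysis restricted to measurements taken before or on the day of first treatment. It should not be the main analysis: it would shrink groups planned at only 50 for AQP4-IgG+ON and MOG-IgG+ON, and may select patients by centre logistics.

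The cost is wording, a check of the data fields and a few more model parameters. One exploratory aim becomes narrower. No new visit or test is needed.
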